### Follow-up visits

#### Antenatal

The GDM clinics at the recruitment sites routinely follow patients with GDM every 2–4 weeks from diagnosis until delivery. During these clinic visits, participants receive their routine care from their endocrinologist, nurse, maternal-fetal-medicine specialist and dietitian. Participants are then seen by our research team during the same visit if possible to verify and record CPAP adherence, download CGM and capillary blood glucose measurements when appropriate, and assess sleep habits through questionnaires. Figure 1 indicates the specific tests and evaluations that are performed at each scheduled visit.

#### Postnatal

After delivery, neonatal and obstetrical outcomes are abstracted through chart review. All study participants are referred to the Sleep Clinic between 1 and 3 months post-partum for assessment of persistent SDB symptoms and a repeat sleep study. Participants also have a follow-up in the GDM clinic with an OGTT to assess for post-partum diabetes and prediabetes. Treatment with CPAP is offered to participants in both groups after delivery until SDB is reassessed at the postnatal Sleep Clinic visit.

### Outcomes

The primary outcome in this study is to objectively determine the adherence to CPAP among women with GDM and SDB. Acceptable adherence is defined by mean usage ≥4 h/night for at least 70% of nights, the conventional threshold for acceptable CPAP adherence in the general non-pregnant population (40–42, 58). Secondary analyses will examine predictors of CPAP adherence (i.e., demographic and SDB severity variables).As a secondary outcome, the suitability of nasal dilator strips as a possible control intervention for a future large-scale, multi-centered RCT in GDM will be assessed. Patient adherence, changes in indices of SDB as assessed by level 2 polysomnography, and changes in sleep quality and daytime sleepiness (questionnaire-based assessments) will be measured.Recruitment and retention rates will be computed at the end of the trial. This will be important in planning a future large scale RCT.The feasibility of measuring glucose levels using CGM in CPAP vs. control groups is also being assessed. CGM provides in-depth information on glucose levels that cannot be obtained from routine blood glucose measurements. We use the well-validated iPro2® (Medtronic, Northridge, CA) CGM (59, 60), a small, minimally invasive device with a painless, subcutaneous sensor measuring interstitial glucose levels every 5 min. These levels are comparable to venous blood glucose measurements (61–63). A trained technician inserts the CGM device subcutaneously in the arm or abdomen, which takes measurements over 3 days to take into consideration day-to-day variability (64). CGM has been used in pregnant subjects previously and is well-tolerated (65). The CGM is blinded so participants cannot see glucose values and will be not be burdened by alarms or sensor inaccuracy. To ensure accuracy of the measurements, CGM requires calibration against capillary blood glucose measurements that are measured as part of standard of care 4 times/day by the participant (61). Insulin requirements are documented at each visit using self-reported insulin doses in patient logbooks. Participants are asked to maintain their usual diet and exercise patterns during this time. Glucose levels between the treatment and control groups will be compared.

### Other assessments

#### Sleep quality and duration

Short sleep duration and sleep quality are also assessed, as these can be additional factors contributing to glucose dysregulation (66, 67). The Pittsburgh Sleep Quality Questionnaire (PSQI) (68) Berlin Questionnaire (69) and Epworth Sleepiness Scale (70) are administered at baseline, and again at weeks 2 and 6 after treatment initiation. Sleep time is objectively measured with the Sensewear® Armband (BodyMedia), which uses an actigraphy analysis to record movements for estimating sleep-wake activity. This Armband is worn for 1 week both at baseline and 1 month after treatment initiation. The pilot study is intended to assess the feasibility of performing these measurements in the pregnant GDM population with SDB.

#### Activity and diet assessments

Dietary habits, including self-reported total energy intake and macronutrients consumed (e.g., fats, protein, carbohydrates) are assessed through routine clinically-administered dietary logs that are monitored by the clinic dietician every 2 weeks. Body weight is recorded at each visit. Moreover, we also measure levels of physical activity through the Sensewear® Armband analysis, which is validated for and measures levels of physical activity (steps, average mets, and energy expenditure) (71, 72). The Armband is worn for 1 week at baseline and after treatment initiation as indicated in Figure 1.

#### Maternal-fetal outcome data

The medical records for each participant is reviewed to obtain data regarding the perinatal course, including details on labor and delivery, post-partum complications, and the course and complications in the newborn.

### Sample size

The assumption underlying the calculation of the sample size was that for CPAP to be an acceptable treatment option in pregnant women with GDM, the adherence should be similar to that observed in the non-pregnant population. Interventional studies with CPAP in non-pregnant populations have demonstrated a wide range of adherence rates [46–83% (73, 74)], with a few recent trials demonstrating adherence rates of ≥60–70% (40, 41). We estimate that 30 participants (CPAP group) will be needed to observe a CPAP adherence rate of 70% with a confidence interval of width of 0.34 or less with probability > 90%. In Table 1, the confidence interval width for CPAP adherence is estimated based on various sample sizes that may be achieved with the pilot trial, with a probability >90%.

**Table 1 T1:** Confidence interval widths for achieving CPAP adherence rates of 70% based on sample size per group achieved in pilot trial.

**Sample size**	**Confidence interval width, with probability >0.90**
20	0.36
25	0.36
30	0.34

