### Data analysis

Between-group differences will be assessed for statistical significance with the Student's *t*-test for normally distributed variables and the non-parametric Mann-Whitney test for non-normal distributions. Continuous variables will be reported as mean ± standard deviation. Median and interquartile ranges will be used for non-normally distributed variables. The primary outcome assesses CPAP adherence, which will be reported as % acceptable adherence rates with associated 95% confidence intervals (using conventional definition of ≥4 h/night for >70% of nights) in participants randomized to the CPAP intervention group. Adherence in the control group will be calculated as the proportion of nights the Breathe Right strips are used (total number of strips used from box over period of treatment nights). Secondary analyses will include the predictors of CPAP acceptable adherence in this population (e.g., demographic and SDB severity variables, SDB sleep symptoms). Recruitment rates will be calculated as the number of participants randomized at each site over the enrolment period. Retention rates will be 100 minus the percent of participants that dropped out after randomization over the period of the trial. Missing data will be analyzed by multiple imputation.

For examination of between-group differences in glycemic control, an intention-to-treat analysis is planned. At baseline and follow-up assessments, mean (standard deviation) 24 h, daytime, and nighttime glucose values will be computed as well as time that glucose levels are above 7.8 mmol/L (hyperglycemia). Between-group differences in change in glycemic control will be calculated with 95% CI. Secondary analyses will estimate linear regressions and adjust for relevant covariates (age, sex, BMI, baseline AHI, baseline glucose).

To minimize bias in interpreting results, the statistician and researchers involved in outcome assessment during data collection and analyses will be blinded to treatment arm allocation.

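### Table 1 states a confidence-interval width of 0.36 at n = 20; standard 95% intervals need at least 0.40 for the stated probability (minor)

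*Protocol article*

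**What the plan says.** The Sample size section of the protocol article justifies the trial's size by precision alone. "We estimate that 30 participants (CPAP group) will be needed" to see an adherence rate of 70% "with a confidence interval of width of 0.34 or less with probability > 90" per cent.

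Table 1 then shows what smaller groups would give. Its caption is "Confidence interval widths for achieving CPAP adherence rates of 70% based on sample size per group achieved in pilot trial" and its column is headed "Confidence interval width, with probability >0.90". The three rows are:

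| n | Stated width |
|---|---|
| 20 | 0.36 |
| 25 | 0.36 |
| 30 | 0.34 |

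This section gives neither the confidence level nor the type of binomial interval. The Data analysis section supplies the level for the same outcome, which is to be "reported as % acceptable adherence rates with associated 95% confidence intervals".

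**The concern.** At a fixed rate, level and probability, an interval for a proportion narrows roughly as 1/√n. Twenty and 25 participants should therefore not share one width. Scaling the n = 25 value back gives 0.36 × √(25/20) = 0.40 at n = 20.

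The table is there to show the precision available if the CPAP group falls short of 30, and n = 20 is its largest shortfall. As printed, it tells the reader that stopping at 20 instead of 25 costs no precision. Adherence is the primary outcome, and the Introduction says that it must be established before larger trials can be powered, so the precision attached to it should be stated correctly.

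**Working it through.** **Inputs.** True adherence rate 0.70, n = 20, 25 and 30, and probability above 0.90 (Sample size and Table 1). Confidence level 95% (Data analysis). Two-sided intervals are an assumption. The interval type is not stated, so the usual ones were all tried.

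**Method.** Let X ~ Bin(n, 0.70). Compute the interval width for every possible x, then find the smallest width w with P(width ≤ w) > 0.90. For the Wilson interval, with p = x/n and z = 1.96,

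width = [2z / (1 + z²/n)] × √[p(1 − p)/n + z²/(4n²)].

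**Step 1: reproduce the rows that can be reproduced.**

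- n = 25: the limiting outcome is x = 15 (p = 0.60). Width = (3.920 / 1.1537) × √(0.00960 + 0.00154) = 3.398 × 0.1055 = 0.359. P(width ≤ 0.359) = 0.904. This is the stated 0.36. Agresti-Coull also gives 0.359.
- n = 30: the Wilson width met with more than 90% probability is 0.331, and the largest Wilson width for any x is 0.337. The stated 0.34 or less is therefore met with probability 1.00.

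**Step 2: the n = 20 row with the same Wilson interval.**

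| Adherent of 20 | Wilson width | P(width no larger than this) |
|---|---|---|
| 15 | 0.357 | 0.416 |
| 14 | 0.373 | 0.608 |
| 12 | 0.395 | 0.892 |
| 11 | 0.400 | 0.969 |

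The 90% mark is first passed at x = 11 (p = 0.55): (3.920 / 1.1921) × √(0.01238 + 0.00240) = 3.288 × 0.1216 = 0.400. A width of 0.36 or less needs at least 15 of 20 adherent, which has probability 0.416. Even the expected result, 14 of 20, gives 0.373.

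**Step 3: other 95% intervals at n = 20.**

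| Interval | Width met with probability > 0.90 | P(width ≤ 0.36) |
|---|---|---|
| Wilson | 0.400 | 0.416 |
| Agresti-Coull | 0.400 | 0.238 |
| Uniform-prior Bayes | 0.403 | 0.416 |
| Jeffreys (equal-tailed) | 0.411 | 0.238 |
| Mid-P | 0.421 | 0.238 |
| Wald | 0.436 | 0.238 |
| Clopper-Pearson | 0.454 | 0.107 |

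Continuity-corrected versions are wide too: 0.441 for Wilson and 0.486 for Wald.

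**Step 4: other readings of the table.**

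- 90% confidence: mid-P gives 0.358 at n = 20, but then 0.317 and 0.290 at n = 25 and 30. Wilson gives 0.344, 0.307 and 0.282. Neither set matches the table.
- Expected width: the mean Wilson width is 0.364 at n = 20 but 0.332 at n = 25, so this does not give the same figure for both rows, and it is not what the column heading says.

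None of the readings tried makes all three rows right.

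**The case against.** The strongest reply is that this is one cell in a contingency table. The trial is sized on 30 participants, not 20, and the error touches no planned sample size, outcome, test or decision rule. The final report will show the interval actually obtained. In half-widths the difference is about 18 against 20 percentage points (0.36/2 and 0.40/2). All of this stands, and it is why the point is minor. It does not make the cell correct.

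A second reply is that the Sample size section states no confidence level. That is true, and the 95% is carried over from Data analysis. It is the level at which the same proportion will be reported, and a 90% level does not reproduce the table.

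A reader might go further and infer that the n = 30 statement is also wrong, because it fails for two common intervals: P(width ≤ 0.34) is 0.73 for Wald and 0.43 for Clopper-Pearson. The document does not support that inference. It names neither of those intervals, and the statement holds for Wilson and Agresti-Coull (1.00) and for Jeffreys (0.92). The choice of binomial interval is a detail normally left to the statistical analysis plan, so its absence here is not a fault.

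Nor does the document show that Wilson was the planning method. It fits the n = 25 row, but at n = 30 it gives 0.33, which agrees with the printed 0.34 only as an upper bound. That the n = 20 cell was copied from the row below is plausible but cannot be shown.

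**Conclusion.** The n = 20 entry in Table 1 is wrong as written. At 70% adherence, a two-sided 95% interval meets a width of 0.40 at best with more than 90% probability, and up to 0.44 (Wald) or 0.45 (Clopper-Pearson) with other common choices. The stated 0.36 is met with probability 0.42 at most, against the claimed 0.90.

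The conclusion assumes that the 95% level in Data analysis applies to Table 1. It does not depend on which of the standard intervals was used. Severity is minor: the planned n = 30 and its 0.34 figure are supportable, and the design and the primary analysis are unaffected.

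**What to change.** Recompute the n = 20 row with whatever method produced the other two rows, and restate it. If that method was Wilson or Agresti-Coull, the entry becomes 0.40; the n = 25 entry stays at 0.36, and n = 30 comes to 0.33, within the stated 0.34.

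As a side note, reporting the primary outcome with a Wilson-type interval would keep the 0.34 figure at n = 30, whereas Wald or Clopper-Pearson would not keep it with the stated probability.

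The cost is one table cell and a slightly less favourable fallback precision.

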### Data analysis

Between-group differences will be assessed for statistical significance with the Student's *t*-test for normally distributed variables and the non-parametric Mann-Whitney test for non-normal distributions. Continuous variables will be reported as mean ± standard deviation. Median and interquartile ranges will be used for non-normally distributed variables. The primary outcome assesses CPAP adherence, which will be reported as % acceptable adherence rates with associated 95% confidence intervals (using conventional definition of ≥4 h/night for >70% of nights) in participants randomized to the CPAP intervention group. Adherence in the control group will be calculated as the proportion of nights the Breathe Right strips are used (total number of strips used from box over period of treatment nights). Secondary analyses will include the predictors of CPAP acceptable adherence in this population (e.g., demographic and SDB severity variables, SDB sleep symptoms). Recruitment rates will be calculated as the number of participants randomized at each site over the enrolment period. Retention rates will be 100 minus the percent of participants that dropped out after randomization over the period of the trial. Missing data will be analyzed by multiple imputation.

For examination of between-group differences in glycemic control, an intention-to-treat analysis is planned. At baseline and follow-up assessments, mean (standard deviation) 24 h, daytime, and nighttime glucose values will be computed as well as time that glucose levels are above 7.8 mmol/L (hyperglycemia). Between-group differences in change in glycemic control will be calculated with 95% CI. Secondary analyses will estimate linear regressions and adjust for relevant covariates (age, sex, BMI, baseline AHI, baseline glucose).

To minimize bias in interpreting results, the statistician and researchers involved in outcome assessment during data collection and analyses will be blinded to treatment arm allocation.

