## Abstract

**Background:** Gestational diabetes (GDM) is associated with adverse short- and long-term maternal and fetal outcomes. Observational data support a link between sleep-disordered breathing (SDB) during pregnancy and GDM. However, it is unknown whether treatment of SDB with continuous positive airway pressure (CPAP) improves glucose control in this patient population. In addition, CPAP adherence and feasibility as a treatment option in pregnancy is unknown. This pilot randomized, controlled trial aims to primarily determine the feasibility of CPAP treatment in pregnant women with SDB and GDM. This study is also investigating the effect of SDB treatment on 24-h glucose profiles as an exploratory outcome.

**Objectives:** To describe the study methodology in this ongoing study of pregnant women with GDM and SDB.

**Patients and Methods:** Pregnant women with GDM and SDB defined by apnea-hypopnea index (AHI) ≥10 (Chicago Scoring Criteria) on level 2 polysomnography are randomized to either auto titrating CPAP (experimental group) or a nasal dilator strip (control group) until delivery. The primary outcome, objectively-assessed adherence to CPAP, is measured over the course of the treatment period using device-specific software. Recruitment and retention rates will be calculated to assess the feasibility for planning future trials. Twenty-four hour glucose profiles are measured over a 72-h period using the continuous glucose monitoring (CGM) system, before and after the intervention.

**Conclusion:** The results of this study will be highly informative to determine whether CPAP is a feasible treatment for pregnant women with GDM and SDB, a specialized population at risk for substantial comorbidity. The trial results will ultimately be useful in planning future SDB treatment trials in pregnancy and GDM.

The study is registered on clinicaltrials.gov (NCT02245659).

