### Treatment interventions

#### Experimental group

Nightly CPAP treatment until delivery: In the participants randomized to the active intervention arm, auto-titrated CPAP (auto-CPAP) is started within 2 weeks of the initial GDM clinic visit following a positive sleep study for SDB. Active arm participants receive an individualized 1 h session on set-up, mask-fitting and preference, and potential side-effects (e.g., dry mouth, nasal congestion). A variety of nasal masks are initially tried for comfort during set-up, but if mouth-breathing, or intolerance to the nasal mask occurs, an oronasal mask is fitted. Education, troubleshooting of side effects occurs every 2 weeks, and more often as necessary by telephone or in-person visits. Download of the CPAP adherence data (adherence, leaks, pressure settings, efficacy with residual AHI) occurs either by Wi-Fi using available software or by interrogation of the memory chip at specific visits every 2 weeks (Figure 1) (56). All participants assigned to CPAP are encouraged to use the device for the remaining period of pregnancy (~8 weeks) for as many hours during sleep as possible.

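### The blanket multiple-imputation rule does not exempt the primary CPAP adherence outcome, so as written it could credit use to women who have left treatment

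*Protocol article*

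**What the plan says.** The Abstract fixes what is measured: "The primary outcome, objectively-assessed adherence to CPAP, is measured over the course of the treatment period using device-specific software". Under Experimental group, CPAP is assigned nightly until delivery, for about 8 weeks, and the adherence download "occurs either by Wi-Fi using available software or by interrogation of the memory chip at specific visits every 2 weeks".

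The Outcomes section sets the criterion: "Acceptable adherence is defined by mean usage ≥4 h/night for at least 70% of nights". The Data analysis section restates it ("using conventional definition of ≥4 h/night for >70% of nights") and reports the percentage meeting it, with a 95% confidence interval, "in participants randomized to the CPAP intervention group". Neither section says over which nights the 70% is taken for a woman who leaves before delivery.

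The same Data analysis paragraph then defines retention, "Retention rates will be 100 minus the percent of participants that dropped out after randomization over the period of the trial", and closes with "Missing data will be analyzed by multiple imputation". No variable is exempted and no imputation model is given. Intention-to-treat is mentioned only for the glycemic comparison in the next paragraph.

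**The concern.** For most outcomes, a value lost after withdrawal is unknown and imputation is a reasonable way to handle it. Adherence is different. Once a woman has withdrawn or handed back the machine, her use on the remaining assigned nights is zero, and that non-use is what the trial sets out to measure. Standard imputation under missing-at-random would instead model her on women who are still supplying downloads and give her some chance of being adherent. When she has in fact fallen short of the criterion, that error can only push the rate up, and it grows with the number who leave.

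The adherence rate is the main product of this pilot. The Introduction says it must be established before larger trials can be powered, so an inflated rate would carry into the next design. Low adherence is a realistic prospect: the Introduction cites a 2-week trial in women with GDM in which 7 of 15 on CPAP were adherent (47%), and this trial asks for about four times that duration.

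**Working it through.** **Inputs from the article.** CPAP arm n = 30, expected adherence 70%, and interval width at most 0.34 with probability above 0.90 (Sample size). Treatment of about 8 weeks, so 8 × 7 = 56 nights (Experimental group).

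**Assumptions, because the article gives no figure.** Share of the CPAP arm with a missing adherence outcome, d = 10% to 30%. Imputed probability of adherence for those women, q = 0.70 (a model with no informative predictors) or q = 0.20 (a model in which poor early use pulls the probability down).

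**1. The planned precision.** Enumerating X ~ Bin(30, 0.7) and taking the 95% interval width at each X, the 90th percentile of width is 0.331 by Wilson (largest width 0.337, so always within 0.34) and 0.337 by Jeffreys (probability 0.916 of being within 0.34). The stated 0.34 therefore reproduces with these methods. It does not with Wald (0.351, probability 0.73) or Clopper-Pearson (0.367, probability 0.43). The half-width used as a yardstick is 0.34 / 2 = 0.17.

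**2. Inflation.** Let p be the adherence rate among women with data.

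- Rate with imputation ≈ (1 − d)p + dq
- Rate with the missing women counted as non-adherent = (1 − d)p
- Difference = dq

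With p = 0.70:

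| d | Counted as non-adherent | Imputed, q = 0.70 | Inflation | Imputed, q = 0.20 | Inflation |
|---|---|---|---|---|---|
| 10% | 63% | 70% | 7 points | 65% | 2 points |
| 20% | 56% | 70% | 14 points | 60% | 4 points |
| 30% | 49% | 70% | 21 points | 55% | 6 points |

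If every woman's use is recorded to delivery, or off-treatment nights are counted as zero, the inflation is 0.

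**3. In whole women.** Suppose 24 of 30 have data and 17 are adherent. The observed rate is 17/24 = 70.8% (Wilson 95% CI 50.8-85.1%), and imputation without predictors returns about the same figure. If the other six count as non-adherent, the rate is 17/30 = 56.7% (39.2-72.6%).

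**4. The nights denominator.** A woman who meets 4 h on each of 28 nights and then withdraws scores 28/28 = 100% on observed nights but 28/56 = 50% on assigned nights. She passes or fails depending on a rule the article does not state. Since 0.70 × 56 = 39.2, she needs 40 nights (40/56 = 71.4%; 39/56 = 69.6%). A woman who leaves after 40 such nights still meets the criterion with the rest counted as zero. Step 2 treats every missing woman as failing, so it overstates the inflation to the extent that some leave late.

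**The case against.** The strongest reply is that the article never says adherence will be imputed for women who leave. It is a condensed account, and which variables are imputed, and what counts as missing, may be settled in a fuller document that is not shown. That is fair as far as it goes: a reader might infer that the plan will impute adherence for these women, and the text does not establish it. What stands is that the article does state a rule, in the primary-outcome paragraph and without restriction, and as worded the rule covers that outcome.

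A reader might also infer that every woman who quits CPAP becomes a missing value. The documents point the other way. Use is recorded by the device and downloaded every 2 weeks, so a woman who stops but keeps the machine has zero use on record, and a returned device should still hold the earlier nights. Only women who withdraw, return the device or have no later downloads are exposed.

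On size, the two-weekly downloads supply exactly the early-use data that a sensible imputation model would include, so 7-21 points is the upper end of the range. This is correct, and it is why the lower figures stand beside it.

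It can further be said that retention is reported separately, so dropout would be visible; that no go/no-go threshold is set; and that 49-63% still lies inside the 46-83% range cited for non-pregnant populations. All true. But reporting retention does not correct the adherence rate, and against the 60-70% or more cited from recent trials, a move from 56% to 70% would change how the result reads.

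Finally, a reader might extend the point to questionnaires given "again at weeks 2 and 6 after treatment initiation", for women who deliver before week 6. The documents do not support this: they give no delivery timing and do not class an assessment falling after delivery as missing.

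**Conclusion.** The concern holds in a limited form. The only missing-data rule is unrestricted, the primary adherence outcome is not exempted, and nothing states that nights after withdrawal or device return are non-use. Applied as written under missing-at-random, the rule would bias the primary rate upward for a defined subset of the CPAP arm.

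The size is conditional. It runs from zero, through about 2-6 points, to about 7-21 points, depending on an assumed 10-30% dropout with no recoverable outcome, an assumed imputed probability of 0.20 or 0.70, and the women concerned falling short of the criterion on assigned nights. The upper figures are comparable with the planned half-width of about 17 points, and the lower ones are well inside it. The direction is clear from the text, but the amount cannot be fixed from it. The documents do not support a claim that the plan as a whole will make poor feasibility look acceptable.

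**What to change.** Amend the missing-data sentence so that it does not apply to the primary outcome, and add a short rule for adherence:

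- Keep the denominator already stated, all women randomised to CPAP.
- Assess the 70%-of-nights criterion over all nights from treatment assignment to delivery.
- Count nights after stopping, withdrawal or device return as 0 h.
- Impute only nights lost for technical reasons, such as device or memory-chip failure, in women still on treatment.
- Report the imputed and observed-data rates as sensitivity analyses.

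Multiple imputation can stay for the other outcomes. The cost is one paragraph of text and no new measurements; the rule needs the dates of withdrawal or device return and of delivery, and obstetrical data are already taken from chart review. The downside is that the reported adherence rate may come out slightly less favourable.

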### Participants

Participants are screened for eligibility if they are pregnant women aged ≥18 years referred to the GDM clinic between >20 and <34 weeks gestational age with a diagnosis of GDM. Participants receive a diagnosis of GDM prior to their first study visit based on a positive non-fasting screening 50-g glucose load (24–28 weeks gestation) of >11.1 mmol/L. If this test is abnormal but not in the diabetic range (7.8–11.1 mmol/L), then a fasting, standard, 75-g oral glucose tolerance test (OGTT) is ordered. GDM is defined at our center with either an abnormal 50-g screening test with level ≥11.1 mmol/L or from one of the following from the 75-g OGTT: (1) fasting glucose ≥5.1 mmol/L, (2) 1-h glucose ≥10.0 mmol/L, or (3) 2-hr glucose ≥8.5 mmol/L (49), all in the absence of pre-existing or pregestational diabetes. Screening questions on snoring, witnessed apneas or other symptoms of SDB are not used in the selection process. Participants are not eligible if they had multiple pregnancy, current cigarette smoking or alcohol consumption, chronic renal disease, cardiovascular disease, stroke, active psychiatric disease, active malignancy, HIV infection, Hepatitis C or B, prior treatment for SDB, occupation involving shift work or travel across time zones, or inability to provide informed consent.

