### Randomization

Eligible participants are randomized using web-based randomization with permuted blocks of varying size (Dacima software, Montreal, Quebec).

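### The lead glycaemic estimate is a between-group difference in change, with baseline adjustment left to a secondary regression that also lists sex, a constant here; ANCOVA would be more precise at no cost

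*Protocol article*

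**What the plan says.** All of the glycaemic analysis is in the Data analysis section of the protocol article. Mean 24-hour, daytime and nighttime glucose, and time above 7.8 mmol/L, are computed at baseline and at follow-up. The contrast is then fixed as follows: "Between-group differences in change in glycemic control will be calculated with 95% CI". No covariate is attached to it. The section's general rule for group comparisons is a two-sample one: Student's t-test "for normally distributed variables and the non-parametric Mann-Whitney test for non-normal distributions".

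Adjustment follows as a lower-ranked step: "Secondary analyses will estimate linear regressions and adjust for relevant covariates (age, sex, BMI, baseline AHI, baseline glucose".

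The Participants section describes the women screened as "pregnant women aged ≥18 years referred to the GDM clinic between >20 and <34 weeks gestational age". Randomization is described only as "Eligible participants are randomized using web-based randomization with permuted blocks of varying size"; no stratification factor is stated.

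On the status of the outcome, the Abstract says: "This study is also investigating the effect of SDB treatment on 24-h glucose profiles as an exploratory outcome". The Introduction places it under the secondary aims, as pilot data for sizing a later multi-centre trial whose primary aim is glycaemic control.

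**The concern.** Two things stand out. First, a baseline value of every CGM measure is collected by design, yet the lead contrast uses it only by subtraction. Subtraction fixes the baseline slope at 1. When the correlation between baseline and follow-up is below 1 and the variances are equal, that slope is too steep. The estimate then carries avoidable noise, and any chance difference between arms at baseline passes partly into it.

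Second, the covariate list was evidently not fitted to this population, since sex does not vary.

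At stake is the precision of the headline glucose estimate. The sample size was set on adherence, so nothing in the design reserves precision for glucose, and the article intends these data to inform the next trial.

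**Working it through.** **The plan's own figures.** The article states no SD, correlation, detectable difference or power for glucose. Its only sample-size figure (Sample size section) is 30 women on CPAP, giving a CI of width 0.34 or less for 70% adherence with probability above 90%. That reproduces with a Wilson interval, whose greatest possible width at n = 30 is 0.337, though not with Clopper–Pearson (probability 0.43). It is used here only as the source of n = 30.

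**Inputs.**
- n = 30 per arm: stated for the CPAP arm, assumed equal for control.
- r, the baseline/follow-up correlation: not stated, assumed 0.3 to 0.8.
- Equal SD at baseline and follow-up: assumed.

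**Step 1: precision.** Per-woman variance in the contrast:
- change score: 2(1 − r)SD²
- ANCOVA: (1 − r²)SD²
- ratio, ANCOVA to change: (1 − r²) / [2(1 − r)] = (1 + r)/2

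The CI width ratio is the square root of this. The half-width is 1.96 × √(variance × 2/30), in SD units. The matching ANCOVA sample size is 30 × (1 + r)/2.

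| Assumed r | Variance ratio | CI width ratio | CI narrower by | Half-width, change | Half-width, ANCOVA | ANCOVA n per arm matching 30 |
|---|---|---|---|---|---|---|
| 0.3 | 0.65 | 0.806 | 19% | 0.599 | 0.483 | 19.5 |
| 0.5 | 0.75 | 0.866 | 13% | 0.506 | 0.438 | 22.5 |
| 0.7 | 0.85 | 0.922 | 8% | 0.392 | 0.361 | 25.5 |
| 0.8 | 0.90 | 0.949 | 5% | 0.320 | 0.304 | 27.0 |

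The formula favours ANCOVA for every r below 1, but it treats the slope as known. For a normal baseline, estimating the slope multiplies the ANCOVA variance on average by 1 + 1/(2n − 4) = 1 + 1/56 = 1.018. The ranking then reverses only above r = 2/1.018 − 1, about 0.965.

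**Step 2: chance imbalance.** If the arms differ at baseline by D, the change score is off by (1 − r)D given that imbalance. For D = 0.3 SD this is 0.21, 0.15 and 0.09 SD at r = 0.3, 0.5 and 0.7. The standard error of a baseline difference with 30 per arm is √(2/30) = 0.258 SD, so 0.3 SD is 0.3/0.258 = 1.16 standard errors. A gap at least that large, in either direction, arises in about one trial in four. Averaged over randomizations D is zero, and so is the error.

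**Step 3: sex.** A design matrix with intercept, arm, four varying covariates and a constant sex column has 7 columns and rank 6. The sex coefficient cannot be estimated. Software drops the column and the remaining coefficients are unchanged.

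**The case against.** The strongest reply is that the article already plans a regression adjusting for baseline glucose. The dispute is then over which of two planned analyses leads, for an outcome the Abstract calls exploratory. This narrows the point but does not remove it: the stated headline estimate is still the less precise one, and the adjusted one is ranked below it. It is also fair that the article never calls the change contrast unadjusted. That is inferred from the absence of covariates and from adjustment being labelled secondary.

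The size depends on assumptions. At r = 0.8 the gain is only about 5%, and the variance formula suits mean glucose better than time above 7.8 mmol/L, which may be skewed.

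A reader might infer more than the document supports:
- *That the change score is biased or invalid.* It is neither under randomization. The loss is precision and conditional sensitivity to imbalance.
- *That the next trial could not be sized properly.* SDs at baseline and follow-up are to be reported, and the SD of change can be derived from the CI. The correlation follows, and with it the ANCOVA residual variance. The secondary regression also yields a residual SD.
- *That the sex term damages the model.* It has no numerical effect.
- *That gestational age was wrongly left out, or displaced by sex, with a 14-week spread at baseline CGM.* The 14 weeks (34 − 20) is the referral window. The Figure 1 legend puts diagnostic testing usually at 24 to 28 weeks, and the Experimental group section has women "encouraged to use the device for the remaining period of pregnancy (~8 weeks"). The spread at baseline CGM is not stated and is probably narrower. Entry timing plausibly affects treatment duration, but the article does not show that gestational age predicts CGM glucose here.

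**Conclusion.** The point holds as a modest matter of efficiency plus one plain slip. With equal variances and about 30 women per arm, leading with ANCOVA would narrow the glycaemic 95% CI by about 19%, 13% or 8% at assumed correlations of 0.3, 0.5 or 0.7, and would remove most of the dependence on chance baseline imbalance. The article supplies no correlation, so the range, not any single value, is the finding. Listing sex is an error in the stated model, without numerical consequence. The omission of gestational age is a matter of judgement, not an error. Adherence, the primary outcome, is untouched.

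**What to change.** In the Data analysis section:
- Make the lead glycaemic analysis an ANCOVA of each follow-up CGM measure on arm plus the same measure at baseline, reporting the adjusted difference with 95% CI.
- Keep raw change by arm as a descriptive summary.
- Delete sex from the covariate list of the secondary regression.
- Optionally, consider gestational age at baseline CGM as a covariate in that secondary model. With about 60 women the covariate set should stay small.

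The cost is wording only. Baseline CGM is already collected, gestational age is needed for eligibility, and the lead model adds one parameter. Neither the sample size nor the visit schedule changes.
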